#### Methods in the analysis to handle protocol non-adherence and any statistical methods to handle missing data {20c}

Study populations include the intent-to-treat (ITT) analysis set defined as all randomized patients, and the per-protocol (PP) analysis set defined as all patients in the ITT population without any major protocol deviations. Multiple imputation is used to manage missing values.

#### Plans to give access to the full protocol, participant level-data, and statistical code {31c}

Data are available upon reasonable request. For inquiries about data sharing, please send a request to [contact].

### Oversight and monitoring

#### Composition of the coordinating center and trial steering committee {5d}

The trial steering committee consists of three members, two senior rheumatologists, and a statistician, who will oversee the trial. The committee is independent of the research team, and there is no conflict of interest. Information on the composition, roles, and responsibilities of group providing day-to-day support to the trial is provided below. The trial was designed by a senior rheumatologist. A rheumatologist and two urologists collect clinical data.

#### Composition of the data monitoring committee, its role, and reporting structure {21a}

The data monitoring committee consists of three members, two senior rheumatologists, and a statistician, who will ensure the safety and quality of data. The committee is independent of the research team, and there is no conflict of interest. They will provide regular supervision, hold monthly meetings, and organize a field trip at least once to ensure the trial is carried out smoothly and ethically. Also, a supervisor will ensure the authenticity and integrity of the data. During the visit, they will interview the investigators, check the original research documents and subject registration, and confirm whether the clinical centers comply with the research protocol. Any non-compliance with the agreement will be fully recorded using a violation report form.

#### Adverse event reporting and harms {22}

The drugs used in the study were recommended in the guidelines for diagnosis and treatment of gout/hyperuricemia and its drug therapies will lead to hepatic impairment. Certain patients are administered sodium bicarbonate may be reactions to the gastrointestinal symptoms. Prednisone acetate induces osteoporosis and potentially increasing the risk of subsequent infections.

Symptomatic treatment would be initiated for you if there is an adverse event during the treatment. In case of hepatic impairment, hepatoprotective therapy was administered (e.g., compound glycyrrhizin for injection, silymarin). Certain patients are administered compound azintamide enteric-coated tablets to prevent gastrointestinal side effects caused by sodium bicarbonate. Prednisone acetate induces osteoporosis and potentially increasing the risk of subsequent infections. Once infected, it is necessary to immediately identify the nature of infection, select sensitive drugs in order to rapidly reach the steady range, and at the same time withdraw the dosage of glucocorticoid.

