Another study suggested that the pH value of urine increased from 5.5 to 6.0 by administering sodium bicarbonate (1 g tid) for 3 months in gout patients [7]. Although several urological associations recommended urine alkalization to promote calculi dissolution in nephrolithiasis [8–11], advanced evidence is lacking. Since alkaline urine may increase the risk of hypertension, water-sodium retention, and heart failure, according to the 2020 American College of Rheumatology (ACR) guideline, starting alkalizing urine is not recommended even in cases of stimulated uric acid excretion. Based on the composition, renal calculus is mainly divided into calcified calculi, urate calculi, cystine calculi, and combinations. Typically, nephrolithiasis is assessed by ultrasonography, plain film radiography, tomography, or excretory urography with an intravenous contrast agent [12]. However, none of these methods could identify calculi before treatment. Dual-energy computed tomography (DECT) is a novel non-invasive technique that fundamentally distinguishes the composition of urate calculi. This method has been previously validated in both in vitro and in vivo studies [12–15]. Moreover, it can also be used to calculate the volume of renal calculi. The present study aimed to determine the effect of sodium bicarbonate-alkalized urine on renal calculus in patients with gout.

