#### Research procedures

(1) Screening: In line with 2015 ACR and EULAR criteria and the score system for acute arthritis of gout, B ultrasonography suggests renal calculi. The patients are 18–80 years old.

(2) Enrolment: Each subject will be interviewed by investigators prior to the start of the treatment, and the data would be input into the database along with baseline data. The subjects will be divided into test and control groups according to the treatment, and both groups will be treated for 6 months. Renal calculus volume changes before and after treatment will be observed and recorded, respectively.

(3) Treatment scheme: Test group: sodium bicarbonate 1 g tid combined with febuxostat 40 mg/day and prednisone acetate 5 mg Qd for 12 weeks. Control group: placebo 1 g tid combined with febuxostat 40 mg/day and prednisone acetate 5 mg Qd for 12 weeks.

(4) Laboratory indicators: Vital signs (pulse, blood pressure, temperature, respiration, and gout flares), four physiological indicators of blood lipids (TC, TG, HDL-C, LDL-C), fasting blood glucose, blood routine (RBC, WBC, NEUT, PLT, Hb), urine routine (pH value of urine, PRO, BLD), renal function (BUN, CREA, sUA, EGFR), liver function (ALT, AST, GGT, ALP), erythrocyte sedimentation rate (ESR), C-reactive protein (CRP), and renal DECT (location, size, quantity component of renal calculi).

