##### Secondary outcomes

The volume changes of renal calculi, uric acid changes, and the proportion of patients whose sUA levels are <360 μmol/L, the changes in eGFR, the pH value of urine, and adverse effects after 12 and 24 weeks of treatment. Adverse events will be monitored during the 24 weeks of treatment, including the incidence of hypertension before and after treatment, the incidence of post-treatment edema, and the rate of acute gout attack within 12 weeks. Any adverse reactions that occur during the study will be recorded in the “Adverse Reaction Table,” and the patients will be followed up until symptoms disappear or indicators return to normal. In the event of serious adverse events, necessary measures will be taken immediately to ensure the safety of the subjects. In addition to evaluating the primary and secondary outcomes, safety assessment will be conducted at baseline and at 24 weeks after treatment with respect to blood pressure, respiration, heart rate, blood routine, urine routine, liver and renal function, ESR, CRP, and renal DECT.

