## Discussion

In patients with gout, vascular injury caused by hyperuricemia and the deposition of urate crystals in the medulla is a major cause of substantial kidney damage, increasing the risk of chronic kidney disease and thus exerting a significant impact on the living quality of patients. Xanthine oxidase inhibitors alone are not as effective as alkalizing urine drugs in preventing renal calculi. Commonly used drugs include sodium bicarbonate and potassium sodium hydrogen citrate. However, both drugs give rise to adverse reactions, resulting in poor patient compliance [16]. Furthermore, recommendations by the 2020 ACR and EAU guidelines for the therapy of renal calculi in gout patients by alkalizing urine are controversial [10, 11]. Due to the lack of strong evidence, we have designed a RCT to analyze the effect of urine alkalization on renal calculi in gout patients by evaluating whether the renal calculus volume is reduced after 12 weeks of treatment. This study will provide guidance on the use of accurate medical methods such as urine alkalization for patients, thereby reducing the incidence of gout flares.

Nevertheless, the present study has some limitations. First, the universality of the sample population and the research centers involved in the trial is limited. In order to complete this clinical trial successfully, the selected participants should be local residents from Shenzhen, which will ensure their participation throughout the treatment. Patients with gout combined with renal calculi under investigation may not have urate calculi, as identified by DECT. In addition, the EAU guideline recommends administration of allopurinol during ULT, requiring the sUA level of each case meeting the standard (> 4.0 mmol/day and/or > 380 μmol/L) [11]. Previous studies have shown that gout patients have a high rate of sUA less than 360 μmol/L who have been treated with febuxostat (40 mg/d) in China [17]. Taken together, this clinical trial aims to explore if urine alkalization is suitable for patients with gout combined with renal calculi and whether the associated adverse events can be avoided. Finally, we hope that clinicians and gout patients can focus on the treatment of alkalized urine for renal calculi.

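### The harms section omits the fluid-retention and heart-failure risks that the rationale names, and the listed measurements capture them only partly and are timed after the blinded phase

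*Protocol article*

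**What the plan says.** All references are to the protocol article.

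- **Background and rationale {6a}** states the risks of the intervention: "Since alkaline urine may increase the risk of hypertension, water-sodium retention, and heart failure". It gives these as the reason why one 2020 guideline advises against starting alkalization. It also reports that several urological associations recommend it.
- **Adverse event reporting and harms {22}** says that the study drugs are recommended in gout and hyperuricemia guidelines. For sodium bicarbonate it lists only this: "Certain patients are administered sodium bicarbonate may be reactions to the gastrointestinal symptoms".
- **Secondary outcomes {12}** lists adverse effects at 12 and 24 weeks and adverse-event monitoring over 24 weeks, "including the incidence of hypertension before and after treatment, the incidence of post-treatment edema" and gout attacks. It adds a general record: "Any adverse reactions that occur during the study will be recorded in the “Adverse Reaction Table". A further sentence fixes the timing: "safety assessment will be conducted at baseline and at 24 weeks after treatment with respect to blood pressure, respiration, heart rate", followed by blood and urine routine, liver and renal function, ESR, CRP and renal DECT.
- **Research procedures, item (4)** itemises the measurements: "Vital signs (pulse, blood pressure, temperature, respiration, and gout flares" and then named laboratory components. The renal panel is BUN, creatinine, sUA and eGFR.
- **Intervention description {11a}** stops placebo after week 12, and weeks 13 to 24 are open-label.
- **Discussion** says the trial will explore, among other things, "whether the associated adverse events can be avoided".

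**The concern.** The section that describes expected harms omits all three risks that the rationale attaches to the experimental drug. The outcomes section makes good one of them, hypertension. For the other two the text is thin. Fluid retention is a yes/no edema count, and heart failure has neither a named event nor a measurement of its own.

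Timing adds to this. The only dated safety assessment after baseline is at week 24, when the control arm has been off placebo for 12 weeks and allocation is known. Edema has no stated definition, so it is a judgement that knowledge of treatment can influence.

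At stake is how much the trial can say about the Discussion's question on avoiding adverse events. If few edema cases are seen, the reader could not tell absence of fluid retention from an insensitive measure.

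**Working it through.** **1. Named risks against planned capture**

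| Risk named in {6a} | In harms section {22}? | In Secondary outcomes {12} or Research procedures? |
|---|---|---|
| Hypertension | No | Yes: incidence before and after treatment, and blood pressure measured |
| Water-sodium retention | No | Partly: post-treatment edema, no baseline or definition stated; no body weight or electrolytes listed |
| Heart failure | No | Not named; pulse and respiration are measured, and general adverse-reaction recording applies |

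The hypertension item refers to before and after treatment. The edema item, in the same sentence, refers only to after. Read literally, edema already present at entry could be counted.

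**2. Exposure**

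Input: 1 g three times daily for 24 weeks (Intervention description). Molar masses: NaHCO3 84.0 g/mol, sodium 23.0 g/mol.

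- 3000 mg / 84.0 = 35.7 mmol of sodium, and of bicarbonate, per day.
- 35.7 mmol × 23.0 = 0.82 g of sodium per day.
- 35.7 mmol × 168 days = 6.0 mol over the course.

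Entry is open down to an eGFR of 30 (Exclusion criteria). These figures describe the load. They do not by themselves show harm.

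**3. What an edema count can detect**

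Input: 49 per arm (Sample size {14}), two-sided 5%. The documents give no edema rates, so those used here are assumptions. Power = Φ[(difference − 1.96 × SE0) / SE1], with SE0 from the pooled proportion and SE1 from the two separate proportions.

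For 4% versus 12%:
- SE0 = √(2 × 0.08 × 0.92 / 49) = 0.0548
- SE1 = √((0.04 × 0.96 + 0.12 × 0.88) / 49) = 0.0542
- (0.08 − 1.96 × 0.0548) / 0.0542 = −0.51, so power is about 31%.

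The same formula over other assumed rates:

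| Edema, control vs bicarbonate | Power, 49 per arm |
|---|---|
| 4% vs 8% | 13% |
| 8% vs 16% | 23% |
| 4% vs 12% | 31% |
| 4% vs 16% | 51% |
| 4% vs 20% | 69% |

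At 4% versus 12% the expected counts are about 2 and 6 (49 × 0.04 and 49 × 0.12), so the normal approximation is rough.

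**4. What a weight measurement could detect**

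Detectable difference at 80% power = 2.80 × SD × √(2/49), where 2.80 = 1.96 + 0.84. The SD of change is an assumption.

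- SD 1.5 kg: 0.85 kg
- SD 2 kg: 2.80 × 2 × 0.202 = 1.13 kg
- SD 3 kg: 1.70 kg

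The documents do not link a weight difference to an edema rate. The comparison therefore shows only that a continuous measure gives usable precision at this sample size, where a rare yes/no event does not.

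**The case against.** A reader might infer that the named harms are hardly measured at all. The documents do not support that. Hypertension is a prespecified outcome with blood pressure behind it, edema is a recognised sign of fluid retention and is counted, and heart rate, respiration and renal function are assessed. Any adverse reaction is to be recorded and followed up, and serious events are provided for. Adverse effects are also listed as an outcome at week 12. A history of heart failure (NYHA II–IV), MI or coronary procedures is an exclusion, so leaving new heart failure to general recording in 98 patients is a defensible choice.

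A reader might also infer that the guideline sentence in {22} is false. That is not shown. The Abstract and rationale cite guidelines in favour, the rationale cites one against, and the Discussion calls the position controversial. The sentence is incomplete rather than demonstrably wrong.

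The absence of body weight and electrolytes can be asserted only for the text at hand. The SPIRIT schedule (Fig. 2) is not shown, and an article condenses the full protocol. The edema item can also be read as meaning new edema, and randomization would tend to balance cases present at entry. Low power for an uncommon event is usual in a trial sized on its primary outcome and is not in itself an error.

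These points limit the concern to hypertension being adequately covered and the rest being incomplete. They do not remove the mismatch between {22} and {6a}, the unnamed heart-failure event, or a dated safety assessment that falls only in the open-label phase.

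**Conclusion.** The harms section is inconsistent with the protocol's own rationale and outcomes section. Capture of fluid retention and heart failure is incomplete in the text shown, but not absent. The improvement is worth making and cheap. It does not affect the primary efficacy comparison.

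On size: with 49 per arm, an edema count has about 31% power for 4% versus 12%, and 13% to 69% over the assumed rates tabulated. Weight change would detect about 1.1 kg at an SD of 2 kg (0.85 to 1.70 kg for SDs of 1.5 to 3 kg). These figures rest on assumed rates and SDs and on all 49 per arm being observed. The textual findings rest on the article alone, and the omission of weight and electrolytes would fall away if Fig. 2 or the full protocol includes them.

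**What to change.** 1. Reconcile {22} with {6a} and {12}: list hypertension, water-sodium retention and heart failure alongside gastrointestinal reactions as risks of sodium bicarbonate, and qualify the guideline sentence to reflect the disagreement that the rationale and Discussion already describe.
2. Record edema at baseline with a stated definition, and count new edema.
3. If the full schedule does not already include them, add body weight at each existing visit, and serum sodium, potassium and bicarbonate to blood draws already planned, including week 12. Weight bears most directly on fluid retention. The electrolytes are the lesser addition.
4. Date the safety assessment at week 12 as well as week 24. Report change to week 12 by arm as the blinded comparison, and report heart-failure events by arm.

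Cost: a short amendment, one weighing per visit and a small laboratory charge, with no extra visits. No treatment rule is proposed.

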#### Frequency and plans for auditing trial conduct {23}

We will audit the trial conduct every 3 months.

##### Plans for communicating important protocol amendments to relevant parties (e.g., trial participants, ethical committees) {25}

Committees will identify the problems in the trial and put forward suggestions on the modification of the protocol. If any decision to amend the protocol has to be made, a written application needs to be submitted to the Institutional Medical Ethics Committee, and the investigator will be notified in writing after approval. The protocol will be updated immediately in the system.

##### Dissemination plans {31a}

All presentations should protect the integrity of the primary research objectives. Any data that compromises the blinding will not be released before the results are available. The steering committee will discuss the recommendations on the timing of these final data that may be presented at the meetings. The primary outcomes will be published in abstract books and articles.

## Discussion

In patients with gout, vascular injury caused by hyperuricemia and the deposition of urate crystals in the medulla is a major cause of substantial kidney damage, increasing the risk of chronic kidney disease and thus exerting a significant impact on the living quality of patients. Xanthine oxidase inhibitors alone are not as effective as alkalizing urine drugs in preventing renal calculi. Commonly used drugs include sodium bicarbonate and potassium sodium hydrogen citrate. However, both drugs give rise to adverse reactions, resulting in poor patient compliance [16]. Furthermore, recommendations by the 2020 ACR and EAU guidelines for the therapy of renal calculi in gout patients by alkalizing urine are controversial [10, 11]. Due to the lack of strong evidence, we have designed a RCT to analyze the effect of urine alkalization on renal calculi in gout patients by evaluating whether the renal calculus volume is reduced after 12 weeks of treatment. This study will provide guidance on the use of accurate medical methods such as urine alkalization for patients, thereby reducing the incidence of gout flares.

Nevertheless, the present study has some limitations. First, the universality of the sample population and the research centers involved in the trial is limited. In order to complete this clinical trial successfully, the selected participants should be local residents from Shenzhen, which will ensure their participation throughout the treatment. Patients with gout combined with renal calculi under investigation may not have urate calculi, as identified by DECT. In addition, the EAU guideline recommends administration of allopurinol during ULT, requiring the sUA level of each case meeting the standard (> 4.0 mmol/day and/or > 380 μmol/L) [11]. Previous studies have shown that gout patients have a high rate of sUA less than 360 μmol/L who have been treated with febuxostat (40 mg/d) in China [17]. Taken together, this clinical trial aims to explore if urine alkalization is suitable for patients with gout combined with renal calculi and whether the associated adverse events can be avoided. Finally, we hope that clinicians and gout patients can focus on the treatment of alkalized urine for renal calculi.

### Trial status

The revised version V20210423 of this protocol on April 23, 2021, has been approved by the Institutional Medical Ethics Committee of Shenzhen Traditional Chinese Medicine Hospital and People’s Hospital of Longhua District Shenzhen. The recruitment will begin on July 1, 2021, and this study will be completed on June 30, 2023.

## Abbreviations

RCT: Randomized controlled trial
ACR: American College of Rheumatology
EULAR: European League Against Rheumatism
MSU: Monosodium urate crystals
ESRD: End-stage renal disease
DECT: Dual-energy computer tomography
OR: Odds ratio
HR: Hazard ratio
CI: Confidence interval
ULT: Urate-lowering treatment
eGFR: Estimated glomerular filtration rate
sUA: Serum uric acid
ESR: Erythrocyte sedimentation rate
CRP: C-reactive protein
ITT: Intent-to-treat
PP: Per-protocol
ANOVA: Analysis of variance
